#### Patient Surveys

RAs will send participants an email with the link to access the web-based structured survey, which will be programmed in Snap Professional software. All data were entered into Snap Professional software. Once the survey is complete (ie, the submit button is selected), the survey is uploaded automatically to the Snap web host. As soon as this transfer is complete, the survey and its data are automatically removed from the device. We will collect whole blood using a finger-stick procedure and use the microfluid sample for dried blood spot analysis.

#### Measures for Aim 2

In addition to basic demographic data that will be used to describe the sample (eg, age, gender, relationship status), we will use the measures summarized below to assess key variables necessary to address aim 2:

The sure test indicates *the probability that a patient experiences clinically significant decisional conflict.*The stage of decision making is a 4-6 item instrument. *Stage of decision making refers to the individual’s readiness to engage in decision making, progress in making a choice, and receptivity to considering or re-considering options.*The Decisional Conflict Scale is a 16-item tool.* The Decisional Conflict Scale (DCS) measures personal perceptions of: (1) uncertainty in choosing options, (2) modifiable factors contributing to uncertainty such as feeling uninformed, unclear about personal values and unsupported in decision making; and (3) effective decision making (in full version) such as feeling the choice is informed, values-based, likely to be implemented and expressing satisfaction with the choice.*The Decision Preparation Scale is a 10-item scale. *The scale assesses a patient’s perception of how useful a decision aid or other decision support intervention is in preparing the respondent to communicate with their practitioner at a consultation visit and making a health decision.*The Health Care Climate Questionnaire (HCCQ) is a 15-item questionnaire. *The HCCQ was designed to be used by patients to report their perceptions of their doctors or their team of health care providers*The PrEP Self-Regulation Questionnaire is a 15-item questionnaire that elicits information regarding why an individual may initiate and/or maintain PrEP usage.The PrEP Use Perceived Competence Scale is a 4-item scale for individuals who elect to use PrEP regarding their perceived confidence to adhere to their decision to use PrEP.

### Payment for Participation

We will implement a modest, modular incentive structure to be applied to participants who enroll and attempt to participate in the study (Table 1). In aim 1, a Can $30 (US $22) cash gratuity will be offered for a 1-hour interview. Health care providers will receive Can $40 (US $29) for the health care provider survey. Participants can receive up to Can $120 (US $86) in aim 2. Participants will be provided with 2 Toronto Transit Commission transit tokens for in-person interviews (enrollment interview and 60-day visit for the finger-stick blood drop). The baseline in-person survey and registration process are expected to take approximately 45 min. The subsequent web-based surveys are expected to take about 15 min; thus, participants in aim 2 are committing to participating for about 1.5 hours of their time. Participants will receive the incentive for enrolling in and completing the study and will also receive it even if they decide (at any point) that they do not wish to continue completing the study activities. If participants know that they will receive the incentive even if they do not complete the procedure (eg, follow-up assessments), then this will reduce the risk that participants are financially coerced to complete any component of the study. These gratuities are also culturally accepted gestures of appreciation for the participants’ generosity in contributing their time and knowledge to the study. Participants will receive incentives immediately after the completion of data collection.

The data collected in this study will not be made available to participants. The data are for exploratory research purposes and are not appropriate for participants to use for medical self-management.

**Table 1 table1:** Participant incentive schedule.

Study procedures		Incentive amount	
**Aim 1 study procedures**			
	Key informant review		Can $30 (US $22)
	Health care provider survey		Can $40 (US $29)
**Aim 2 study procedures**			
	Baseline survey		Can $20 (US $15)
	14-day follow-up		Can $30 (US $22)
	30-day follow-up		Can $30 (US $22)
	60-day follow-up		Can $40 (US $29)

### Subject Withdrawals

We will advise all study participants that their involvement in the study is completely voluntary and that they are free to withdraw at any time, for any reason, without penalty or prejudice. This will be emphasized during the process of obtaining initial informed consent from participants and again during each of the data collection points of the study. Participants who withdraw from the study will be provided with an opportunity to indicate if they also want any data collected up to that point to be used in the study analysis. If a participant does not wish to have their data included in the study analysis, then we will identify the specific data in our database and mark it as *999=not for use in analysis.* We will also keep a record of reasons for participant withdrawals (if the participant wishes to disclose such reasons), to monitor patterns and use these in our research team training sessions to better identify strategies to support retention.

### Risk/Benefit Assessment

#### Risks to Subjects

Participation in the study does not involve more than minimal risk. Potential risks of study participation are outlined as follows.

#### Frustration With Assessments

Potential risks of participation in the study include the frustration that may be encountered in completing assessments, scales, and questionnaires. Subjects are carefully counseled that they may discontinue testing at any time if they find it frustrating or embarrassing. There is also a potential risk of breaching patient confidentiality.

#### Risk for Financial Coercion

We will also implement a modest, modular gratuity structure to be applied to participants who enroll and attempt to participate in the study. A Can $30 (US $22) cash gratuity will be offered for participation in the key informant interview. Health care providers who participate in the structured survey will receive Can $40 (US $29) cash gratuity. Subjects who participated in the pilot trial will receive a modest gratuity at enrollment when they register on the decision aid app via their smartphone device (Can $25 [US $18]), at day 30 when they complete the midpoint survey (Can $30 [US $22]), and at day 60 (Can $45 [US $32]) when they provide a blood sample for adherence assessment. Although the gratuity is very modest, it is possible that some individuals experiencing severe material and financial deprivation may be compelled to participate against their own volition in order to receive the modest gratuities offered.

#### Risks of Unintentional Disclosure of Private Health Information

The greatest potential risk in this study was the potential for a breach of confidentiality which is most likely to occur in situations where the participant has opted to have the RA perform study procedures (eg, study description, informed consent, data collection) outside of one of the participating agencies, such as in their private home. The clinic sites are all equipped with private examination rooms that allow the participant and RA to discuss private health information without the risk of unauthorized persons overhearing protected information. To support participant autonomy and comfort, we will also designate the SMH Li Ka Shing Knowledge Institute as an alternative site for data collection. This site also has private spaces where study procedures can be performed. If a participant desires to complete study procedures in a nonclinic location, the RA cannot guarantee that what is discussed cannot be overheard by others who may be in the immediate vicinity either at a fixed distance away or moving around nearby.

### Legal Implications of Unintentional Disclosure of Private Health Information

It is possible that the participants in this study could be engaged in social and/or legal contractual arrangements with others that may presume mutual monogamy, such as marriage. An unintentional disclosure of sexual behavior information, including same-sex behavior, could provide material evidence for litigation against the study participant by an allegedly injured party. This could have both legal and financial consequences for the study participants. This risk is more likely to occur during a visit outside of the clinical setting where others who are not bound by privacy regulations may be in close enough proximity to hear clinical discussions between the participant and the RA.

### Protections Against Risk and Minimizing Risk of Unintentional Disclosure of Private Health Information

#### Emphasis on Voluntary Nature of the Study

We will emphasize to all study participants that their involvement in the study is completely voluntary and that they are free to withdraw at any time, for any reason, without penalty. This will be emphasized during the process of obtaining initial informed consent from participants and again before enrollment and data collection. Participants who withdraw from the study will be provided with an opportunity to indicate whether they also want any data collected up to that point to be used in the study analysis. We will also keep a record of reasons for participant withdrawals (if the participant wishes to disclose such reasons), such that we can try to monitor patterns and use these in our research team training sessions to better identify strategies to support study retention.

#### Use of Emergency Protocols for Patients Experiencing Psychological Distress

During the course of the study, it may become apparent that a participant is experiencing psychological distress of some sort that warrants further clinical assessment and possibly intervention. This distress could be experienced at any time during the course of the study. However, there is very little evidence to support that behavioral and psychosocial surveys trigger acute episodes of psychological distress for study participants in behavioral research studies; nonetheless, it is remotely possible. If a participant appears to be in psychological distress during the interview, the RA will bring the interview to a close. After that, they will sensitively engage the individual to determine if they wish to talk about what causes them distress. The RA will also ask questions to ascertain if the participant is receiving any support for their distress (eg, friends, family, or professionals), and if not, whether they feel they would benefit from support. If they wish to receive support, the RA will provide them with a list of professionals to talk to.

It is more likely that a participant may experience distress upon receiving an HIV diagnosis. After initiating contact with the RA, participants will be provided with the Canadian AIDS Treatment Information Exchange (CATIE)’s contact information, including their website. CATIE is a nationally respected Non Governmental Organization⸺funded federally and provincially⸺that provides evidence-informed, sex-positive, plain language HIV and Hepatitis C resources in French and English, in print, via phone, and through collect calls. We do not know how many (if any) participants will HIV seroconvert during the course of their participation in the study. All participating clinics have many years of experience in planning for and responding to situations in which patients are unable to manage their psychological distress and require support from clinical staff. We will use clinical site-specific security and emergency protocols to handle potential situations that arise at the site.

#### Reminder About Risks of Disclosures Outside of Clinic Environments

If a participant wishes to provide informed consent and survey procedures outside of the SMH FHT’s, SMH Li Ka Shing Knowledge Institute, or community agency study sites, we will remind them of the limitations this poses for maintaining confidentiality. We will further inform the participant that even if no one is physically present at the location they choose, we cannot guarantee the degree to which the discussion of any clinical information is *private*. We will remind participants that they are not compelled to share any information about which they do not feel comfortable. We will also advise participants of the advantages of study procedures to take place in the preapproved study sites. We want participants to be forthcoming with their information; however, they will be reminded that they are not compelled to share any information that they feel may jeopardize their health or social status.

#### Benefits to Subjects

##### Direct Benefits to Participants

There are no direct benefits to the participants for enrolling in this research study.

##### Benefits to Others

This study has important potential benefits to the community and to primary HIV prevention science. The study will generate knowledge that will be used to inform the development of a decision support intervention to help participants make more informed choices about their engagement in clinical HIV prevention. Furthermore, this proposed study will form a foundation to support more studies of program and implementation science that aims to make scientific advances through research while at the same time making gains and improvements in health outcomes in real-world practice environments.

#### Important Knowledge to Be Gained

Results from this pilot will generate data for the preliminary studies section of a research grant application. The results will also help us determine how providing decision-support and improving decision quality can enhance local health department efforts to link and support black patients’ maintenance of HIV PrEP.

#### Alternatives to Participation

In this study, participants chose to withdraw their participation at any time. To our knowledge, there are no alternatives for PrEP-related decision support available in the GTA. There are several clinic-based and web-based resources that provide information regarding HIV PrEP. Participants can make use of any available sources of PrEP information via the agency from which they were referred. Any participant who wishes to discontinue participation in the study will be offered a leaflet that lists HIV PrEP informational resources.

#### Confidentiality of Data and Information Storage

We will only collect the minimum contact information necessary to be able to reach participants for scheduling and reminders about the study visits and data collection. We will collect a participant’s first name (or alias), cell phone number, and email addresses. We will not collect information such as home address and work phone number so as to avoid the risk that unauthorized persons can apprehend and use it to identify study participants. We will also ask participants to provide the number of 1-2 trusted family members or friends that we can call in the event of a medical or legal emergency, or if we are unable to reach the participant for a follow-up. We will not provide family or friend contacts with any information about the study to maintain participant confidentiality.

The study team will use electronics-based surveys using the Snap Professional software for data collection. Please note that the Snap Professional Software has been reviewed and approved for use by St. Michael Hospital’s: [name], Manager of Privacy and Security and [name], Research Applications Support Specialist (Information Communication Technology). The Snap server utilized is owned by the Centre for Urban Health Solution Survey Research Unit and is located inside the SMH network.

No identifiable participant information or de-identified participant information will be stored locally. The RA will not record any client contact information in the Snap Professional software. Original lab reports (source documentation) will be stored onsite at the SMH lab and maintained by the site principal investigator (LN) at SMH when the study concludes.

All survey data were entered into Snap Professional software. Once the survey is complete (ie, the submit button is selected), the survey is uploaded automatically to the Snap web host. Before it reaches the web host, it must first travel through a secure socket layer (SSL), which is where the data is encrypted. Any partially completed surveys will undergo the same process and can be retrieved from the web host to complete at a later date. As soon as this transfer is complete, the survey and its data are automatically removed from the device. Data stored on the secure web host server will be deleted after study completion. Before deletion, the research team will confirm that all completed surveys have been downloaded to the SMH secure server. Once confirmed, the surveys will be deleted from the Snap webhost, and this will be documented in an Excel file. Again, both the Snap web host and SSL tunnel have undergone a TRA to ensure that the data transferred and stored remains encrypted and secure.

No identifying information (eg, name, address, phone number, place of employment) was collected in the behavioral survey. The behavioral survey data is maintained separately from the data file, which includes participants’ contact information to reduce the risk that survey responses are linked to participant identities. No identifying information is listed on the blood samples of the dried blood spots. The dried blood spot transport media will be labeled only with participant identification codes. ID codes will be used to match the emtricitabine/tenofovir concentration with the self-report data variables for each participant.

#### Research Information in Medical Records

No information generated during the study will become part of the participant’s medical record, unless requested by the participant. If such a request is posed by the participant, they will be advised of the potential risks and benefits to doing so. The request will be honored, provided it does not transgress the privacy and confidentiality requirements of Ontario.

No one outside of the principal investigator, RA, research manager, study medical director, and a medical provider with a clinical *need to know* will have access to any identifiable data. The RA will need access to basic identifying data such as name and phone number for follow-up contact purposes to aid in recruitment, enrollment, and data collection. If an urgent clinical issue arises (such as a participant experiencing acute psychological distress), it may be necessary to link a participant’s contact information to the subject’s identity in order to provide clinical follow-up. No data will be shared without the participant’s written informed consent to release medical information. It is in keeping with the principle of beneficence to ensure continuity of care by making it possible (not mandatory) for participants to share information with the medical provider.

#### Data Analysis and Data Monitoring

##### Planned Statistical Analysis

###### Aim 1: Analysis Plan

Interview data will be transcribed verbatim and subjected to qualitative content analysis. After uploading the transcripts into NVivo, we will read each transcript and use *in vivo* (open) coding function to bracket text segments that describe factors that influence decision-making regarding PrEP adoption. We will also develop *a priori* codes based on SDT constructs and use these, along with open codes, to investigate research questions. We will use data display tables to arrange codes by decision-group (adopted vs declined vs undecided) and examine the text associated with each code, consolidating overlapping codes and clustering codes that fit together. The code clusters will be reviewed within and across decision groups to interpret and describe how they address our research questions. We have successfully used these analytic strategies in previous qualitative research.

###### Aim 2: Analysis Plan

To compare conditions, we will use analysis of covariance procedures. When we compare the 4 conditions, our primary interest will be the tests of participants who received the decision-support intervention versus the information-only control. We will test whether the decision quality, PrEP initiation, and PrEP adherence differ between conditions controlling for baseline decision-quality score. We did not conduct a power analysis to calculate sample size because we de-emphasized hypothesis testing in favor of generating effect size estimates to inform the development of a larger study.

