### Objectives

We propose 2 aims to address these gaps in HIV prevention and implementation science:

Adapting the Ottawa Decision Support Framework (ODSF) for use in the PrEP decisional needs of black patients (Multimedia Appendix 2).Pilot testing the decision support intervention using a 2-arm randomized design to estimate effect size compared with the control condition in reducing decision conflict and predicting adherence over 60 days.

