### Aim 2: Methods and Study Procedures

#### Aim 2: Pilot Test of the Adapted Decision-Support Intervention Using a 2-Arm Randomized Controlled Design

Hypothesis testing will be deemphasized in favor of generating effect size estimates. This aim will investigate 3 research questions. Preliminary hypotheses include the following:

H1: PrEP decision support reduces decision conflict in both low decisional conflict (LDC) and high decisional conflict (HDC) groups.H2: LDC + decision support group will be more likely to initiate PrEP than LDC control.H3: LDC PrEP initiators are more likely than HDC PrEP initiators to have serum levels consistent with adherence at 60 days.

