#### Pilot Procedures

We will use C4 decision support tool, which is an HTML-5 mobile web-based app that does not require device-specific configurations. Staff will provide participants with a web link to the decision-support app. When possible (ie, when a participant has a smartphone or other applicable device), staff will help participants preprogram the decision support app as both a bookmark and an icon on the participant’s device and the RA will give participants a brief tutorial on its use. Patients assigned to the experimental condition (High Decision Conflict + Decision Support and Low Decision Conflict + Decision Support) will be asked to use the bookmarked link to the decision-support website within the first 14 days (and thereafter as needed) during the study period. The routine care control group will be asked to use a bookmarked link to the frequently asked questions website on emtricitabine/tenofovir for PrEP. All groups will be compared on decision readiness and decision conflict at 14 days, self-reported PrEP initiation at 30 days, and PrEP adherence at 60 days postenrollment.

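### The one stated aim 2 model adjusts H3's low- versus high-conflict adherence contrast for a baseline decision score that may be the grouping variable itself

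*Protocol article*

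**What the plan says.** The protocol article, Aim 2: Analysis Plan, names one method, "To compare conditions, we will use analysis of covariance procedures", and one covariate, which it applies to all three outcomes: "We will test whether the decision quality, PrEP initiation, and PrEP adherence differ between conditions controlling for baseline decision-quality score". It then gives the contrast of main interest: "When we compare the 4 conditions, our primary interest will be the tests of participants who received the decision-support intervention versus the information-only control".

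The four conditions are decisional-conflict level crossed with arm. Pilot Procedures describes two of them: "Patients assigned to the experimental condition (High Decision Conflict + Decision Support and Low Decision Conflict + Decision Support". Under Randomization, only experimental versus control is randomised; conflict level is not.

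The aim 2 hypotheses include one that is not an arm comparison: "H3: LDC PrEP initiators are more likely than HDC PrEP initiators to have serum levels consistent with adherence at 60 days".

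No section states which instrument, cut-off or time point defines LDC and HDC, or which instrument gives the decision-quality score. Measures for Aim 2 lists the SURE test, the 16-item Decisional Conflict Scale and other scales, and links none of them to either term.

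**The concern.** A model that contains both a grouping and the score from which the grouping was cut does not estimate the difference between the groups. It estimates what remains of that difference among people with the same score, which amounts to a jump at the cut-point. H3 asserts the plain difference.

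The text gives four reasons to suspect this overlap:

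- H1 expects decision support to lower conflict in both the LDC and the HDC group, so the groups must exist before the intervention acts. A grouping on baseline conflict is the natural reading.
- Pilot Procedures lists the outcomes as readiness and conflict ("All groups will be compared on decision readiness and decision conflict at 14 days"), then initiation, then adherence. The analysis plan lists decision quality, initiation and adherence. Decision quality stands where conflict stood.
- The Background names the link between decision quality and adherence as an evidence gap. H3 is the only hypothesis that links a decision measure to adherence, and it uses LDC/HDC.
- No listed instrument is called decision quality. The full Decisional Conflict Scale, which includes an effective-decision component, is the closest description.

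The pilot exists to supply effect sizes for a larger study. An H3 estimate that has been shrunk by the model, or made very imprecise, would be carried into that design.

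**Working it through.** The protocol gives no effect size, power or adjusted contrast, so there is no figure of its own to reproduce.

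**Inputs from the protocol.** Aim 2 has 40 participants; the model is ANCOVA with a baseline decision-quality covariate; H3 contrasts LDC with HDC among initiators.

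**Assumptions.** The baseline score is standard normal. Adherence falls 0.5 per SD of conflict, with residual SD 1. The split is 50/50 unless stated. The number of initiators is not given, so 12 to 40 is used.

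**1. Overlap of a score with its own cut.** With share p in the HDC group and cut-point c, r = φ(c)/√(p(1−p)) and the variance inflation factor is VIF = 1/(1−r²).

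- p = 0.5: r = 0.399/0.5 = 0.798; VIF = 1/(1−0.637) = 2.75; SE multiplier √2.75 = 1.66.
- p = 0.2: r = 0.280/0.4 = 0.70; VIF = 1/(1−0.49) = 1.96; SE multiplier √1.96 = 1.40.

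**2. Size of the contrast, same score, linear relation.** The two halves differ in mean score by 2 × 0.798 = 1.596, so the unadjusted LDC−HDC difference is 0.5 × 1.596 = 0.80. Once the score is in the model, expected adherence depends on the score alone, so the LDC coefficient is 0. Simulation gives 0.80 and 0.00. The adjusted value also stays at zero when the score measures true conflict with reliability 0.6 or 0.8.

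With binary adherence (69% versus 40%, logistic slope 0.8 per SD), the log odds ratio falls from 1.22 to 0.05 and the risk difference from 0.29 to 0.04.

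**3. Other readings that the text allows (simulated).**

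| Relation of cut to covariate | Share of contrast kept |
|---|---|
| Same score, linear | 0% |
| Same score, true step at the cut | 100% |
| Different scores, adherence follows the cutting score; correlation 0.9 / 0.7 / 0.5 | 39% / 75% / 89% |
| Different scores reflecting one trait; correlation 0.9 / 0.7 / 0.5 | 21% / 44% / 59% |

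**4. Precision of the H3 contrast, same score, linear relation (simulated SE).**

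| Initiators | Unadjusted | Adjusted |
|---|---|---|
| 12 | 0.64 | 1.12 |
| 20 | 0.48 | 0.81 |
| 30 | 0.39 | 0.63 |
| 40 | 0.34 | 0.54 |

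Under a true step, 20 initiators give 0.80 both ways, but the SE rises from 0.47 to 0.80, as large as the effect itself.

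**5. The randomised contrast.** With 40 participants and a true arm effect of 0.50, the estimate is 0.50 with and without the covariate. The SE falls from 0.35 to 0.33 with it.

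**The case against.** The strongest reply is that the protocol never says that the LDC/HDC cut and the decision-quality score are one measure. The section on evidence for adapting the Ottawa framework treats resolving decisional conflict as one of several ways to improve decision making, so decision quality may be a broader idea. The SURE test is described as an indicator of clinically significant conflict, so a different instrument or a genuine threshold is possible. This stands: a reader might infer that H3 is adjusted to zero whatever the instruments are, and the documents do not support that.

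A reader might also take the Objectives phrase, "compared with the control condition in reducing decision conflict and predicting adherence over 60 days", to mean that adherence is to be predicted from conflict. As worded it describes intervention against control, so the point rests on H3 and not on that phrase.

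Third, the stated primary interest is the arm comparison, where baseline adjustment is standard and, by step 5, harmless. H3 is a preliminary, non-randomised hypothesis in a small pilot that plays down testing. This also stands, and it limits the weight of the point.

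The reply that the model for H3 can be left to a fuller document does not stand. The article fixes a covariate for adherence across all conditions and exempts nothing. Followed as written, that rule is applied to H3.

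**Conclusion.** The concern holds in conditional form and for H3 only. The stated rule estimates LDC versus HDC at equal baseline decision score, which is not what H3 asserts if the score and the cut are the same or closely related measures. The loss then ranges from complete (same score, linear relation: 0.80 SD to about 0) through partial (21% to 89% kept at correlations of 0.5 to 0.9) to none in size but much in precision (true step at the cut). With the same score, the SE rises about 1.4 times at a 20/80 split and 1.66 times at 50/50.

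A reader might infer that the whole aim 2 analysis is compromised. It is not: the randomised contrast, and with it H1 and H2, is not biased by the covariate. Identity of the two measures is an inference from the text, and every effect size used here is an assumption.

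**What to change.** Change the H3 analysis only, in one of two ways:

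- leave out the baseline decision score and compare LDC with HDC initiators, adjusting for arm; or
- regress adherence on the continuous baseline decisional-conflict score, adjusting for arm, in place of the LDC/HDC cut.

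Report either as a non-randomised association among initiators. Naming the instrument behind the LDC/HDC cut and behind the decision-quality score would show which row of the table in step 3 applies. Keep the baseline covariate for the comparison of decision support with control.

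Under the linear, same-score assumption, this restores the H3 difference from about 0 to about 0.80 SD and lowers its SE from 0.81 to 0.48 with 20 initiators, or from 0.54 to 0.34 if all 40 initiate.

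The cost is wording. The decisional-conflict measures are already listed, and at the time of writing aim 2 had not started. The downside is that H3 is then openly labelled observational, which it already is by design.
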